#### Wechat operation

WeChat is the intervention medium for this study. The researchers will establish WeChat groups and created WeChat official account before the intervention. The researcher will send the completed content of the WeChat official account to the participants on the WeChat social platform. Participants can use the chat box function of the WeChat social platform to provide feedback and exchange on content of the WeChat official account, and can also interact with other participants in the WeChat group to share their self-management experience and personal insights on health knowledge. And they are required to use this application to inform researchers of their fasting blood glucose level, postprandial blood glucose level, hypoglycemia, diet and exercise status (Fig. 3).

**Fig. 3 Fig3:**
[figure not shown]
Flowchart of the Wechat operation for SISMT for DM-MCI

### Control group

The control group will adopt the HMI. After the outpatient service, health education will be given to patients. We will provide patients with disease-related health manuals to help with the self-management of patients. The content of the health manual revolves around the epidemiological status, diagnostic methods, clinical manifestations, influencing factors, and intervention methods of cognitive impairment. Distribute a health manual and explain it to each participant in the control group. Outcome indicators will be collected at three time points: baseline, 12 and 24 weeks, respectively.

### Criteria for discontinuing or modifying

During the intervention period, if the participant is unwilling to continue due to personal reasons, the intervention will be terminated. Participants who are unable to continue but are willing to undergo follow-up will be modified for intervention measures and replaced with a control group.

### Adherence of intervention

Firstly, WeChat is adopted as the intervention medium and a multifunctional social media application in our study. Researchers can request participants to provide feedback and clock in on the intervention content to test the adherence of the intervention implementation. Secondly, Wechat official account has background data (the number of times and number of readers read), which can monitor the learning of participants. When the data does not match the number of participants, it will remind them in the Wechat group. Thirdly, establishing good cooperative relationships with participants fundamentally ensures adherence.

### Concomitant care

During the intervention process, participants should continue to take medication related to the disease. And inform patients before the intervention begins that they cannot participate in other intervention activities during the participation process. However, if participants participate in other interventions targeting outcome indicators such as blood glucose control and cognitive function during the participation process, their test data will be excluded.

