### Sample size calculation

The required sample size is estimated using PASS v11.0 (NCSS, Kaysville, UT, USA) based on a completely random design for comparing the means of two independent samples. To our knowledge, there is no previous study on a stratified support pattern-based internet-assisted self-management therapy for DM-MCI in mainland China, so we estimate the effect size of one of the outcomes (HbA1c) based on previous research on patients with DM-MCI [42]. This study find that HbA1c scores in intervention and control group are 6.49 ± 1.59 and 6.97 ± 0.73, respectively. A sample size of 34 participants per group was determined to be sufficient to detect an effect with a type 1 error rate of 5% (α = 0.05) and 90% power (β = 0.1). A total of 68 participants will be needed, with 34 participants per group. Considering a 20% loss of follow-up rate, the final sample size is 86, with 43 participants per group.

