### Randomization, blinding, and concealed allocation

Ensuring allocation concealment, participants will be randomized (after obtaining written informed consent, eligibility screening, and baseline assessment) to the intervention and control groups at a 1:1 ratio by a study staff member (who will not be involved in participant recruitment or outcome assessment) using Research Randomizer software (http://www.randomizer.org/). Participants in the intervention group will be assigned to different categories of the intervention group based on their cognitive function and self-management characteristics and will receive Intervention measures with different frequencies. Participants in the control group will be assigned to different categories of the control group based on their cognitive function and self-management characteristics, too, but there is no difference in intervention frequency. The participants will then be told their group assignment by the intervention staff. Due to the nature of non-pharmacological interventions, only the outcome assessors and data analysts (not the participants or intervention staff) will be blinded to group allocation.

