### Statistical analysis

All data analysis will be performed using SPSS Statistics v21.0 (IBM). To ensure that they are blinded to group assignment, the outcome assessors and data analysts will not interact with the participants except during data collection (in the case of outcome assessors). Demographic and other baseline characteristics will be summarized using descriptive statistics. If necessary, the results will be adjusted for potential confounders, such as age, gender, and education. Quantitative data will be expressed as frequencies or rates and statistical analysis will be carried out using the *χ*^2^ test. If these data are normally distributed, they will be expressed as (*x* ± *s*). The effects of the interventions (between-group differences) will be calculated with linear mixed models using interaction terms (group allocation versus time), which are equivalent to the between-group differences. The within-group differences will be calculated using repeated measures ANOVA. *P*-values < 0.05 will be considered statistically significant. The data will be reviewed before analysis. The Statistical Package for the Social Sciences (SPSS) software will be used for all analyses. The clinical relevance of the results will be confirmed by calculating the effect size (Cohen d) of the significant differences found between the assessments. The following effects will be considered: small: 0.00–0.49; medium: 0.50–0.79; high ≥0.80 (Cohen, 1988). Comparison between the four subgroups within the intervention group using ANOVA test.

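### Excluding the data of randomised participants who join another programme can bias the between-group comparison, and the rule for those who cannot continue does not say in which arm they are analysed

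*Protocol article*

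**What the plan says.** **Exclusion rule.** Under Concomitant care, patients are told before the intervention starts that they may not join other intervention activities. If they nevertheless join ones "targeting outcome indicators such as blood glucose control and cognitive function during the participation process, their test data will be excluded". The rule covers both arms. It is not limited to data collected after the event, and it is not confined to a sensitivity analysis or a per-protocol set.

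**Rule for those who cannot continue.** Under Criteria for discontinuing or modifying, participants who cannot go on but accept follow-up "will be modified for intervention measures and replaced with a control group". The section does not mention analysis.

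**Timing and knowledge of the arm.** Under Randomization, blinding, and concealed allocation, "participants will be randomized (after obtaining written informed consent, eligibility screening, and baseline assessment"), so both rules act on people already randomised. The same section says "The participants will then be told their group assignment by the intervention staff" and that "only the outcome assessors and data analysts (not the participants or intervention staff) will be blinded to group allocation". The abstract says allocation is hidden from participants as well. The Methods section is the specific one, and it says the opposite.

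**Analysis.** Under Statistical analysis, the effect is estimated with "linear mixed models using interaction terms (group allocation versus time), which are equivalent to the between-group differences". The primary outcomes are MoCA and MMSE, and the primary hypothesis concerns 12 weeks.

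**The concern.** Randomisation makes the two arms comparable as they were formed. Removing people because of something they did afterwards keeps that comparability only if the removal is unrelated to arm and prognosis, and here there are reasons to doubt it. Controls receive a manual and an explanation of it, while SISMT participants receive reminders, knowledge checks and consultation over WeChat. The wish to look for other help can therefore differ by arm. So can the chance that staff hear of it, because SISMT participants report glucose, diet and exercise to the researchers.

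The deleted values are measured outcomes, not unavoidable losses. No model choice restores them: a mixed model by allocated group cannot use data that have been taken out. At stake is the validity of the primary cognitive comparison at 12 weeks, and of every secondary comparison subject to the same rule.

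**Working it through.** The plan gives no rate of exclusion or switching and no prognosis for those affected. It has no figure for this bias to reproduce, and every share and gap below is an assumption.

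**1. Exclusion rule.** Let p_C and p_S be the shares excluded in the control and SISMT arms. Let δ be the amount, in SD units, by which excluded participants would have scored better than those retained, taken as equal in both arms.

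- Mean of those retained minus full-arm mean = −p × δ in each arm.
- Bias in (SISMT − control) = (p_C − p_S) × δ.
- Assumed p_C = 15%, p_S = 5%, δ = 0.5: 0.10 × 0.5 = 0.05 SD.
- Assumed p_C = 20%, p_S = 5%, δ = 0.8: 0.15 × 0.8 = 0.12 SD.

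The sign follows the assumptions. If those excluded would have done worse (δ negative), or if more are excluded from SISMT, the same figures become −0.05 to −0.12 SD. If shares and gaps are equal in both arms, the bias is zero.

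**2. Scale.** With the plan's 34 evaluable participants per group, the standard error of a simple difference in SD units is √(2/34) = 0.243. The illustrated bias is then 0.05/0.243 = 0.2 to 0.12/0.243 = 0.5 of a standard error. Recruiting more participants would not reduce it.

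**3. Data lost.** The plan's allowance for loss reproduces: 34/(1 − 0.20) = 42.5, rounded up to 43 per group. It covers loss to follow-up only. If a further 10% were excluded under this rule, 34 × 0.90 = 30.6, about 31 per group, would remain. I take 34 as stated; whether it follows from the HbA1c inputs is a separate question.

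**4. The rule for those who cannot continue, under its two readings.** Suppose a share f of each arm is of the kind that could not continue. Only those in SISMT can be affected by the rule.

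- *Counted as controls.* Assume no true effect and that these participants do g SD worse. SISMT loses them, so its mean is 0. Control already holds its own such participants and gains the others, so its mean is −2fg/(1 + f). The apparent benefit is 2fg/(1 + f). With 4 of 43 (f = 0.093) and g = 0.5 this is 0.085 SD; with 6 of 43 (f = 0.140) and g = 0.8 it is 0.196 SD.
- *Control care only, analysed as allocated.* Assume these participants gain nothing from SISMT. The estimate is then (1 − f) times the effect in the others: 1 − 4/43 = 0.91 or 1 − 6/43 = 0.86 of it. This is dilution, and the randomised comparison is intact.

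The two readings have opposite consequences, and the text does not choose between them.

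**The case against.** **The warning given beforehand.** Patients in both arms are told not to join other activities. This should make such events rarer and is a reason to think the assumed shares are high. It does not change what happens to the data when an event occurs.

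**Analysis by group allocation.** The mixed model uses group allocation, the same term the randomisation section uses for the assigned arm, and formal analysis sets are commonly left to the statistical analysis plan. This is fair, and the lack of an explicit intention-to-treat statement is not the point here. The point is an exclusion that the protocol itself states, which an analysis plan following it would inherit.

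**Only later data may be dropped.** The article does not say whether all of a participant's data go. If only data after the event go, the mixed model keeps the earlier visits, which limits the harm. But for an event before 12 weeks only baseline would remain, and the primary value would still be missing because of behaviour after randomisation.

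**Participants who cannot continue.** The section concerns delivery of treatment, and its wording may well mean only that control care replaces SISMT measures. A reader might infer that the protocol moves these people into the control arm for analysis. The text allows that reading but does not establish it, and it gives no reason for being unable to continue, so worse prognosis is also an assumption.

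**Direction.** A reader might infer that both rules favour SISMT. The documents do not support this. Controls may seek help because they are getting worse, in which case excluding them flatters the control arm. Outside programmes may also come to light more often among SISMT participants, through their WeChat contact. And on the control-care reading, the second rule shrinks the effect.

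**Conclusion.** The concern holds for the exclusion rule. As written, it selects on behaviour after randomisation by participants who know their arm, and it discards observed outcomes. It can bias the primary comparison by an amount and in a direction that the documents do not determine. The range of 0.05 to 0.12 SD, in either direction, is an illustration that rests wholly on assumed exclusion shares and an assumed prognosis gap. I do not express it as a fraction of the plan's effect size, because the only one available is for HbA1c, a secondary outcome, while the primary outcomes are MoCA and MMSE.

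The rule for participants who cannot continue is an ambiguity to resolve, not a proven fault. The figures of 0.085 to 0.196 SD apply only if such participants are counted as controls and do worse as assumed.

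**What to change.** 1. Under Concomitant care, replace the exclusion with: *All randomised participants are analysed in the arm to which they were randomised, with all collected data, whatever other intervention they receive or join.*
2. Record in both arms, by the same procedure, any other programme joined and its date. Apply the exclusion only in a labelled per-protocol sensitivity analysis.
3. Under Criteria for discontinuing or modifying, add that a participant whose intervention is modified remains in the randomised arm for analysis. This concerns analysis only and leaves open what care the participant receives.

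The cost is two sentences and a short record of co-interventions. The planned sample size does not change. The downside is some dilution of the estimate from co-intervention and non-adherence, which the sensitivity analysis can help to describe.

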### Outcomes

#### Outcome measures timeline

To compare the outcomes of the self-management interventions provided under the SISMT and HMI, a baseline (W0) survey will be administered to both the experimental and control groups before the start of each pattern. Outcome indicators will be collected 12 weeks (T1) and 24 weeks (T2) after the intervention to compare the effects of the two patterns (Table 2). The indicators will be assessed by experienced staff members who will be blinded to the group allocation. Outcome indicators and measurement tools are as follows (Domains /characteristics of tools see Table 3):

**Table 2 Tab2:**
[figure not shown]
Time schedule of the a stratified support pattern-based internet-assisted self-management therapy for DM-MCI

**Table 3 Tab3:** The domains/characteristics of tools

Tool	Domains/Characteristics
MoCA	Evaluate overall cognitive function; Developed by Nasreddine et al., it is an internationally recognized MCI screening tool that evaluates eight cognitive domains: attention, visual space and executive function, memory, language, abstract thinking, computation, and directional ability. It consists of 12 questions with a total score of 30 points. A score of 26 or higher indicates normal cognition, while a score of higher indicates better cognitive function. If the education period is less than 12 years, a score greater than 25 is considered normal, and the lower the score, the more severe the cognitive impairment of the patient; Detect Cronbach's α Coefficient 0.83, specificity 0.87
MMSE	Evaluate overall cognitive function; MMSE has a total score of 30 points, consisting of 30 items covering 7 cognitive domains: orientation, memory, attention and computation, language, and visual-spatial structure. This scale is used to evaluate the overall cognitive function of the study subjects and can effectively distinguish between normal individuals and elderly individuals with dementia. This study adopts the revised version by Wang Zhengyu et al. and sets an outlier threshold based on educational level. When the illiterate group scores ≤ 17 points, the primary school group scores ≤ 20 points, and the middle school and above group scores ≤ 24 points, it is considered abnormal
AVLT	This study adopts the Chinese version of AVLT developed by Guo Qihao and others from Shanghai Huashan Hospital, which has good reliability and validity and has important application value for clinical guidance and scientific research. The operation of this scale mainly involves the researcher reading 12 words: coat, driver, pants, crabapple, carpenter, lily, headscarf, wintersweet, soldier, magnolia, lawyer, and glove. After each reading, the patient is asked to repeat as many words as possible and record them. The number of repeated words in the 3 times is added as the instant memory quantity (i.e. N1 + N2 + N3); After 5 min, ask the patient to recall 12 words and say if they still remember them. The researcher recorded the number as short-term memory (N4); After 20 min, ask the patient about the number of words they remember as long-delayed memory (N5); Finally, a re-recognition test was conducted, with a total of 24 words and 50% of the vocabulary with 12 interfering items. The patient responded with "said" or "not said", and the researcher determined that each correct answer scored one point
SDMT	SDMT is commonly used for testing attention, learning, and conversion abilities. This test is a numerical symbol subtest in the revised Wechsler Adult Intelligence Revised in China (WAIS-RC), which reflects the information processing speed of the subject. During the testing process, participants were provided with a piece of paper with a template containing 9 digits, each with its corresponding symbol. The test requires patients to fill in as many and as quickly as possible the corresponding numbers of the symbols in the spaces below the numbers. The subjects should fill in as many and correct numbers as possible within 90 s. When it's time to calculate the correct number, the higher the score, the better the tester's attention and conversion ability
SAS	GDS is the SAS Self-Rating Anxiety Scale that was designed and developed by Zung in 1971 in the United States to measure the degree of individual anxiety symptoms. The scale has a total of 20 items, of which 5, 9, 13, 17, and 19 are scored in reverse. The scale adopts a scale of 1–4 (scoring method: 1 point for no or very little time; 2 points for a small portion of time; 3 points for a considerable amount of time; 4 points for the vast majority or all of time). Individuals fill out the scale based on their own situation in the most recent week, multiply the total score by 1.25, take an integer as the standard score, and use it as a statistical indicator. The higher the standard score, the more severe the anxiety level of the individual. The scale score can only serve as a reference indicator for evaluating anxiety and cannot be used for diagnosis
GDS	GDS is used to screen for depressive symptoms in the elderly population and is one of the most commonly used scales in China to evaluate the depressive status of the elderly. This study used GDS-15, which contains 15 items and can be used for rapid screening of elderly people with depressive symptoms. It is an internationally commonly used scale. Define a score of 0–4 as no depressive symptoms, 5–8 as mild depressive symptoms, 9–11 as moderate depressive symptoms, and 12–15 as severe depressive symptoms
MUNSH	This scale is used to measure the current level of happiness experienced by participants; Contains 24 items: each item is a description of emotions or experiences, requiring a response of "yes", "no", or "not knowing" based on recent life experiences; Regardless of whether the item is positive or negative, the answer "yes" is recorded as 2 points, "no" is recorded as 0 points, and "don't know" is recorded as 1 point. All items have a score range of 0 to 24 points, and the total subjective well-being score is equal to the positive item score minus the negative item score, with a value of -24 points to + 24 points. To avoid negative points, the total score is added to a constant of 24 points, and the final score range is 0 to 48 points
QoL-AD	This scale can be used to measure the quality of life of patients with cognitive impairment, reflecting the physiological, psychological, and social relationships, and some complex life abilities of the elderly. The scale consists of 4 dimensions and 13 subordinate items. The 4 dimensions are physical health and behavioral compliance, mental state, living environment and social relationships, and life satisfaction. Each item is scored into four levels, namely poor, average, good, and very good. The score is positively correlated with quality of life, with higher scores indicating higher quality of life. The different criteria are as follows: a QOL-AD score ≤ 26 points indicates a lower quality of life, a QoL-AD score of 27–38 points indicates a moderate quality of life, and a QoL-AD score ≥ 39 points indicates a higher quality of life. The scale Cronbach's α coefficient is 0.66; The intra-group correlation coefficient of the total score is 0.84
GSES	The Chinese version of the General Self-Efficacy Scale was first used in 1995, and some studies have also used GSES to measure self-efficacy in individuals with mild cognitive impairment. The scale consists of 10 items, using the Likert 4-level scoring method. The lowest score is 10 points, and the highest score is 40 points. The higher the score, the better the self-efficacy, that is, the stronger the confidence in dealing with things. The scale has good reliability and validity, Cronbach's α The coefficient ranges from 0.76 to 0.90
SES	This scale was developed by American psychologist Rosenberg in 1965 and has good reliability and validity. This study used the Chinese version of the self-esteem scale revised by Ji Yifu et al., consisting of 10 items, to measure the overall self-esteem level of a single dimension through self-evaluation. Using a four-level scoring system of 1 to 4 points, representing very non-compliant, non compliant, compliant, and very compliant. 1. 2, 4, 6, and 7 are forward counting items, while 3, 5, 8, 9, and 10 are reverse counting items. The total score range is 10 to 40 points, and the higher the total score, the higher the level of self-esteem
HLS	The scale is based on Nutbeam's hierarchical model of health literacy as the theoretical framework to establish an item pool that includes three dimensions: interactive health literacy, critical health literacy, and functional health literacy. There are a total of 19 entries. The content validity index of the total scale is 0.972, and the content validity of each item is 0.83–1.00. Cronbach's α The coefficient is 0.945, with Cronbach's for each dimension α The coefficients are 0 894, 0.909, 0.877. The scale adopts the Likert 5-level scoring method, with scores ranging from "cannot" to "completely possible" ranging from 1–5 points. The higher the total score, the better the level of health literacy
DSCS	Assess the self-management ability of diabetes patients; This scale was developed in 1992 by Hurley and Shea and was simplified into Chinese by domestic scholars Wang Jingxuan et al. Cronbach's α coefficient is 0.92. The scale consists of six dimensions: dietary management, blood glucose monitoring, foot care, exercise management, medication management, prevention, and management of high and low blood sugar. There are a total of 26 items, with a Likert score of 5 points. A score of 1–5 points corresponds to a total score of 26–130. This scale has good reliability and validity when used in both Taiwan and mainland China

